## 11.2 Determination of Sample Size

To calculate the sample size, hypothetical experiments were simulated. We estimate a sensitivity of 99% and a specificity of 98% of non-contrast syngo DynaCT Sine Spin imaging for the detection of intracranial hemorrhage as it was described for the predecessor generation in the literature.^48^ To account for variation, diagnostic performance of hypothetical readers was varied with rates of 98.5%, 99% and 99.5% for sensitivity and 97.5%, 98% and 98.5% for specificity. Rates were attributed randomly with equal chance.

Sensitivities and specificities of readers were generated from correlated binary random variables. To reproduce the correlated readings between readers, a high correlation between binary random variables was chosen. This assumption was made based on the literature and judgement of the principal investigators. We further simulated lower correlations which showed consistently that an approach using a high correlation is more conservative (i.e., leading to a higher sample size). Generated outcomes were vectors with 1 (true positive) and 0 (false negative) for sensitivity and 1 (true negative) and 0 (false positive) for specificity. The quotient of the occurrences of 1 and the number of cases with/or without a bleeding being sensitivity and specificity, respectively. In case sensitivity or specificity was 100%, a false negative (for sensitivity) and a false positive (for specificity) was introduced into the generated output. This enabled to still fit a model (see below).

To represent “difficult cases”, i.e. patients who present with an isolated infratentorial intracranial hemorrhage, we introduced a subpopulation of patients for whom the performance of raters was only 70% sensitivity. We chose n = 14 patients based on an additional sample size calculation. With this subsample, there is an 80% chance (power) that the lower bound of the 95%-CI of a sensitivity of 70% is higher than 50%. However, we assume that the subsample substantially overrepresents the incidence of difficult cases in the study population (see section 6.1). Therefore, we attributed a lower weight in the model to each difficult case.

It was tested whether the lower end of the 95%-CI did not fall below the prespecified margins. For sensitivity and for specificity this was 95%. The 95%-CI of sensitivity and specificity were calculated by fitting a generalized linear random-effects model with a logit link function. Random-effects variables were patient and reader, outcome variable was the randomly generated binary vector. To converge to model estimates, the algorithm of the “nloptwrap”-optimizer was applied.

From the model, the lower end of the 95%-CI of the fixed-effect intercept was extracted and transformed to percent. The 95%-CI was calculated by the method of Wald. If the lower ends of the 95%-CIs of sensitivity and specificity both did not fall below a pre-defined margin, the experiment was rated as “successful”. The percentage of “successful” experiment out of all experiments characterizes the study power. Each sample size, n_i=1,..,19_ = 80,…,260 was evaluated by sampling 999 times n_i_ individual samples with a range of readers from 1 to 7.

If the total weight of “difficult cases” is set at 0.02, the number of difficult cases at n= 14, the power at 90% the number of readers at 6, and the drop-out rate at 5%, a total of **252 patients** (238 patients without drop-outs) must be recruited. The patients must be pre-selected in a ratio of hemorrhage positive to hemorrhage negative of 1:1, i.e., 126 patients are presenting with and 126 patients without intracranial hemorrhage (out of which 14 present with an isolated infratentorial intracranial bleeding). The number of readers was set based on our model calculations since with a lower number of readers the sample size fluctuated substantially (over 100%). The needed sample size however stabilized at a range of 5 to 7 readers. With this number of readers, the sample size fluctuated only by 10% (with 7 readers being the lowest and with 5 the highest).

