2. Although patients will be enrolled based mainly on clinical features, we defined a required number of patients (n = 14) with bleedings which are according to current literature harder to detect on predecessor FDCT generations than on MDCT, i.e. isolated bleedings in the posterior fossa / isolated infratentorial hemorrhages.^39, 48^ This approach was chosen to estimate the diagnostic performance of non-contrast syngo DynaCT Sine Spin imaging also in challenging, rare cases. It therefore allows a broader estimate of its ability for the detection and exclusion of intracranial hemorrhages. However, for the final analysis these cases will have a lower weight as they would have if they were count in by their proportion (14 isolated infratentorial bleedings out of 126 bleeding cases: 11%). In the final analysis they will contribute to the estimate of the sensitivity for the detection of intracranial hemorrhage of FDCT with a fixed weight of 2% (please refer to section 11.5 for a detailed description of the primary analysis). This weight which is lower than their share within the sample size was chosen as from the principal investigators and the US chairs clinical experience (including over 30 years of attending work in neuroradiology/neurosurgery) these cases are very rare (< 1%) in the investigated population and rarely present with symptoms, which would lead to a direct to angiography approach. To further validate their estimated prevalence in the patient group of question (patients with symptoms suggestive of an acute ischemic stroke), we did an analysis of all suspected stroke cases presenting to the University Hospital Basel in the years 2015 to 2019. The data was derived from the Swiss Stroke Registry and included 5,448 patients. Out of these only 48 patients (0.8%) presented with an isolated infratentorial bleeding.

The decision to include 14 isolated infratentorial / posterior fossa bleedings was chosen to be able to generate meaningful data for this bleeding type as well. It assumes that the sensitivity for the detection of these bleedings is 70%. In this case we would have a power of 80% to show that the lower bound of the corresponding 95%-CI interval of the sensitivity for these cases is above 50%. Please refer to section 11 for a detailed description of the calculation of the sample size.

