## 11.3 Readers

There will be 6 experienced readers (board certified neuro-interventionalists) who each rate all sine-spin non-contrast FDCT images on a two-point scale (presence or absence of intracranial hemorrhage). These readers will be selected in a way that they represent readers who typically rate such images in clinical routine setting. It will be secured that they do not work together or were trained together.

The sequence of the images to be read will random and differ for each reader. The readers will be blinded to all clinical data and to the clinical reading. To simulate clinical routine settings, a time limit (90 seconds) will be set for completion of the rating of the FDCT. All ratings will be noted on a standardized form. Ground truth will be deemed based on MDCT as described under 6.1. The reader of the MDCT will differ from the readers of the FDCT and they will not share any information. The number of hemorrhagic strokes and non-hemorrhagic strokes will not be disclosed to the readers.

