### 11.5.3 Secondary Analysis

Fleiss’ kappa will be estimated to assess interrater reliability between 6 readers. Specificity, accuracy, positive predictive value, and negative predictive value will be calculated for FDCT.

For the subset of patients with an isolated infratentorial hemorrhage the sensitivity of FDCT for its detection including its 95%-CI will be reported separately.

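### The 80% power stated for 14 isolated infratentorial cases does not follow from the protocol's inputs; it needs a low reader correlation or an interval that does not hold its level

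*Protocol*

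**What the plan says.** Section 11.2 of the protocol sets the size of the infratentorial subset: "We chose n = 14 patients based on an additional sample size calculation". The result given is that "there is an 80% chance (power) that the lower bound of the 95%-CI of a sensitivity of 70% is higher than 50" per cent. Section 6.1 repeats it, again assuming a sensitivity of 70%: "In this case we would have a power of 80% to show that the lower bound of the corresponding 95%-CI interval" exceeds 50%.

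For this calculation the protocol does not say whether one or six readings per patient were counted, which interval was used, or what correlation between readers was assumed. For the main simulation, section 11.2 says that "a high correlation between binary random variables was chosen" (no value given), that "Random-effects variables were patient and reader, outcome variable was the randomly generated binary vector", and that "The 95%-CI was calculated by the method of Wald". Section 11.3 fixes the number of readings: "There will be 6 experienced readers (board certified neuro-interventionalists) who each rate all sine-spin non-contrast FDCT images on a two-point scale".

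On analysis, section 11.5.3 says: "For the subset of patients with an isolated infratentorial hemorrhage the sensitivity of FDCT for its detection including its 95%-CI will be reported separately". Sections 6.1 and 11.5.2 give these cases a fixed 2% weight in the primary sensitivity estimate.

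**The concern.** Fourteen patients is a small number for separating 70% from 50%, a difference of 20 percentage points when the standard error of a proportion of 0.7 on 14 patients is about 12 points (√(0.21/14) = 0.122). An 80% chance of clearing 50% looks too high unless the 84 readings (14 × 6) count as nearly independent, and the same section describes readings that are strongly alike.

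What is at stake is the justification for the third enrolment bucket and the reading of a separately reported result. Section 6.1 singles these bleeds out as harder to detect on earlier flat-detector systems. Someone told that the subset has 80% power may take a lower bound under 50% as evidence against the device, although such a bound may well be the more likely outcome even if sensitivity is 70% as assumed.

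**Working it through.** **Inputs.** 14 patients, true sensitivity 0.70, threshold 0.50, 95% interval and stated power 80% (sections 6.1 and 11.2); six readers (section 11.3). Assumptions: the interval is two-sided (z = 1.96), and the unquantified correlation ρ is shown over a range.

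**Step 1: one reading per patient.** The Wald lower limit is p̂ − 1.96·√(p̂(1−p̂)/14).

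- 10/14: 0.714 − 1.96 × 0.121 = 0.478, which fails. Wilson (0.454), logit-Wald (0.439) and exact (0.419) limits fail too.
- 11/14: 0.786 − 1.96 × 0.110 = 0.571, which passes. Wilson (0.524) and logit-Wald (0.506) pass; exact (0.492) fails.

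Power at 0.70 is a binomial tail:

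- P(X ≥ 11) = 0.194 + 0.113 + 0.041 + 0.007 = 0.355.
- P(X ≥ 12), needed for the exact interval, = 0.161.

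The most lenient variant, a one-sided 5% Wald limit, accepts 10/14 (limit 0.516) and gives 0.229 + 0.355 = 0.584. No one-reading variant reproduces 80%. The first sample size that does is 40 (Wald), 43 (Wilson) or 49 (exact).

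**Step 2: six readers, design effect.** The effective number of readings is n_eff = 84/(1 + 5ρ), and power ≈ Φ(0.20/√(0.21/n_eff) − 1.96).

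- ρ = 0.2: n_eff = 42; Φ(2.83 − 1.96) = 81%.
- ρ = 0.5: n_eff = 24; Φ(2.14 − 1.96) = 57%.
- ρ = 0.8: n_eff = 16.8; Φ(1.79 − 1.96) = 43%.
- ρ = 1: n_eff = 14; Φ(1.63 − 1.96) = 37%, which is the normal approximation to the 35.5% in step 1.

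**Step 3: six readers, simulation.** Exchangeable beta-binomial readings, 14 patients, lower limit from the mean of the patient-level detection rates and their standard error (40,000 runs per point):

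| ρ | 0.2 | 0.3 | 0.5 | 0.8 | 0.9 |
|---|---|---|---|---|---|
| Power, patient-clustered Wald | 76% | 68% | 56% | 44% | 41% |

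Smaller runs put the last two values at 35–52%, so 41–45% is a fair summary. A t-based limit is lower, at about 49% for ρ = 0.5 and 38% for ρ = 0.8.

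**Step 4: what does return about 80%.**

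- *Low correlation.* ρ near 0.2 by the design-effect formula, and somewhat below 0.2 by simulation.
- *84 readings treated as independent.* At ρ = 0.8–0.9 this gives about 80%. At a true sensitivity of 50%, its lower limit exceeds 50% in 20–22% of runs, against a nominal 2.5%.
- *The protocol's model* (logit, random patient and reader, Wald limit on the intercept). It gives 39–45% at ρ = 0.5 and 73–89% at ρ = 0.8–0.9. At a true 50% it crosses 50% in 24–36% of runs for ρ = 0.8–0.9. The rise goes with unstable fits: the estimated patient standard deviation on the logit scale exceeded 5 in 87% of runs at ρ = 0.8.

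In the same 200-run checks, the patient-clustered interval crossed 50% in about 2–5% of runs. The model results rest on 200–250 runs per point, so carry an error of about 2.5–3.5 points.

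**The case against.** The best defence is that the calculation behind the 14 cases is not shown, and that the protocol's own model with six readers at a correlation of 0.8–0.9 returns roughly the stated figure. On that view the 80% is undocumented rather than miscalculated. The description of high correlation also belongs to the main simulation and carries no number, so carrying it over to the separate calculation is an inference. These points stand, and they limit what can be claimed: a reader might infer from step 3 that power cannot exceed about 55%, but the documents support no such ceiling. They do not rescue the 80%, because a figure obtained from an interval that crosses 50% in a quarter to a third of runs at a true 50% is not power at the stated confidence level.

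Nor is 35% simply the trial's power. It applies to one reading per patient or to readers who agree completely, and the trial has six readers.

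A reader might also expect the 5% drop-out to cut the subset below 14. The protocol largely prevents this: refusals of post-hoc consent (section 2.9), excluded lead-in cases (section 9.2) and withdrawals before outcome assessment (section 11.6) are replaced, and the exclusion for bleeding between scans applies only to patients whose ground truth is negative (section 6.1).

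Finally, no decision rule uses 50%. Section 11.5.3 only reports an estimate with its interval, and the subset has 2% weight in the primary analysis. That bears on severity, not on whether the stated figure is right.

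**Conclusion.** The point holds, with moderate severity. The 80% in sections 6.1 and 11.2 cannot be reproduced from 14 patients, 70% sensitivity and a 95% lower bound above 50%. A correlation of 0.5 or more, which is a fair reading of the word high, puts power at about 40–55% with a patient-clustered interval, and full agreement between readers puts it at about 35%. Only a correlation below about 0.2 brings a sound interval to 80%, and that conflicts with the section's own description. The conclusion rests on a two-sided 95% interval, exchangeable readings and the protocol's description of reader correlation also applying to these cases. It does not extend to the power of the primary analysis, which this calculation does not determine.

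**What to change.** Choose one of two corrections, and make it in both 6.1 and 11.2.

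- Replace the 80% with power recomputed for six readers, stating the correlation used and an interval that accounts for clustering by patient. Expect about 40–55% at a correlation of 0.5 or more, and about 35% if readers agree fully.
- Or drop the power claim and describe the subset as estimation only, with its expected precision. For example, detection in 10 of 14 patients gives a Wilson 95% interval of about 45–88%.

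In either case, use a patient-clustered interval for the infratentorial sensitivity in 11.5.3. The protocol leaves that interval unspecified, so the statistical analysis plan can carry this detail.

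The cost is a text change in two places and one recalculation. No patients are added and the primary analysis is unchanged; the stated figure becomes less favourable.

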## 11.3 Readers

There will be 6 experienced readers (board certified neuro-interventionalists) who each rate all sine-spin non-contrast FDCT images on a two-point scale (presence or absence of intracranial hemorrhage). These readers will be selected in a way that they represent readers who typically rate such images in clinical routine setting. It will be secured that they do not work together or were trained together.

The sequence of the images to be read will random and differ for each reader. The readers will be blinded to all clinical data and to the clinical reading. To simulate clinical routine settings, a time limit (90 seconds) will be set for completion of the rating of the FDCT. All ratings will be noted on a standardized form. Ground truth will be deemed based on MDCT as described under 6.1. The reader of the MDCT will differ from the readers of the FDCT and they will not share any information. The number of hemorrhagic strokes and non-hemorrhagic strokes will not be disclosed to the readers.

## 11.4 Statistical criteria of termination of the investigation

None

## 11.5 Planned Analyses

### 11.5.1 Dataset to be analysed, analysis populations

For the analysis the full analysis set (FAS) will be used. The FAS contains all patients for which the six readers read all non-contrast syngo DynaCT Sine Spin images and rated them on a two-point scale (presence or absence of hemorrhage).

### 11.5.2 Primary Analysis

The primary analysis will be based on the FAS. As described for the sample size calculation, a generalized linear random-effects model with a logit link function will be fit. The explanatory variables ’reader’ and ’patients’ will be random effects. Difficult cases will be weighted with 2%. From the fixed-effect intercept of sensitivity and specificity, the 95%-CIs will be calculated applying the method of Wald. Sensitivity will be calculated based on the results of all core-lab readers of the non-contrast syngo DynaCT Sine Spin scans of all patients for which the ground truth was deemed to be hemorrhage positive. Specificity will be calculated based on the results of all core-lab readers of the non-contrast syngo DynaCT Sine Spin scans of all patients for which the ground truth was deemed to be hemorrhage negative. It will be tested whether both the lower bound of the 95%-CI of the sensitivity and specificity are higher than the margin of 95%.

All results will be reported in concordance with the STARD guidelines.^20^

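### The in-model 2% weight and the intercept read-out do not give the 98:2 sensitivity that section 6.1 declares when readings of a patient are highly correlated

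*Protocol*

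**What the plan says.** Section 6.1 (reason 2 for the design) sets the target. The difficult cases make up 11% of the hemorrhage-positive sample, but they are to "contribute to the estimate of the sensitivity for the detection of intracranial hemorrhage of FDCT with a fixed weight of 2" percent.

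Section 11.2 gives the method used in the power simulation: "Therefore, we attributed a lower weight in the model to each difficult case". The total weight of these cases "is set at 0.02, the number of difficult cases at n= 14". The model is a logit random-effects model: "Random-effects variables were patient and reader, outcome variable was the randomly generated binary vector". The result is read from one parameter: "From the model, the lower end of the 95%-CI of the fixed-effect intercept was extracted and transformed to percent". For the dependence between readers, "a high correlation between binary random variables was chosen", with no figure. Simulated readers had "rates of 98.5%, 99% and 99.5% for sensitivity and 97.5%, 98% and 98.5% for specificity"; the difficult cases had 70% sensitivity.

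Section 11.5.2 carries the same model into the primary analysis. Patient and reader "will be random effects. Difficult cases will be weighted with 2" percent, and the Wald lower limit from the fixed-effect intercept is compared with 95%. Nowhere does the protocol describe a 98:2 combination made outside the model.

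**The concern.** A fixed 2% contribution describes a weighted average of two sensitivities. A logit model with a patient random effect does not produce that average automatically, for two reasons.

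- **The weight.** If it is attached to each reading, it gives 2% only when the six readings of a patient are close to independent. When they nearly repeat one another, down-weighting each reading does little to down-weight the patient.
- **The read-out.** The fixed-effect intercept describes a patient whose random effect is zero. With a large patient variance, its back-transformed value lies well above the average sensitivity, whatever weight is used.

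At stake is what the primary sensitivity claim means. The value compared with 95% would reflect a mix of ordinary and difficult bleeds that depends on reader agreement and on software, not the declared mix. The simulation in 11.2 uses the same construction, so it cannot reveal the mismatch.

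**Working it through.** **The plan's own figures.** 238 evaluable patients at 1:1 is 119 per group. 119/0.95 = 125.3, rounded up to 126; 2 x 126 = 252, as stated. 14/126 = 11.1%, as stated. The step from 90% power to 238 cannot be reproduced exactly, because the correlation is not given.

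**Inputs.** Other evaluable positives: 119 - 14 = 105 (assuming all 14 difficult cases are evaluable). Six readers. Sensitivity 99% (the mean of the three reader rates in 11.2) and 70%. The 2% is taken as a total, as 11.2 says. The within-patient correlation is assumed, 0.05 to 0.8.

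**Target.** 0.98 x 0.99 + 0.02 x 0.70 = 98.42%.

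**Nominal weight.** For a 2% total share, each difficult case or reading has relative weight (0.02/0.98) x 105/14 = 0.153. Six readings at 0.153 add up to 0.92 of one reading.

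**Weight on readings.** A patient-intercept logit model was fitted by numerical integration to expected beta-binomial counts, with the reader effect omitted. Realised share = (0.99 - marginal sensitivity)/(0.99 - 0.70).

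| Correlation | Share of marginal sensitivity | Share of information on the intercept | Score of a difficult case missed by all six, relative to an ordinary one |
|---|---|---|---|
| 0.05 | 2.0% | 2.0% | 0.15 |
| 0.2 | 2.3% | 4.3% | 0.34 |
| 0.4 | 2.9% | 8.3% | 0.52 |
| 0.6 | 4.8% | 14.2% | 0.70 |
| 0.8 | 8.0% | 19.3% | 0.86 |

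At 0.8 the implied marginal sensitivity is 0.99 - 0.080 x 0.29 = 96.68%, against 98.42%. The 2% holds only where the patient effect is about zero.

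**Weight on each patient's marginal likelihood.** The marginal sensitivity is then about 98.4%, a share of about 2%. The tested intercept is 6.1 on the logit scale at correlation 0.05, or 1/(1 + exp(-6.1)) = 99.8%, and 7.9 at 0.2, or 99.96%. It does not behave like an average either: at 0.05, adding the difficult cases raises it from 5.7 (99.7%) to 6.1 (99.8%), although their sensitivity is lower.

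**Software of the kind named in 11.2.** lme4's glmer was run with nloptwrap, crossed patient and reader effects, and reading weight 0.153. Take 105 ordinary cases, one missed by all six readers and one by a single reader: (105 - 1 - 1/6)/105 = 98.89%. Take 14 difficult cases, six missed by all: 8/14 = 57.14%. The 98:2 value is 0.98 x 98.89% + 0.02 x 57.14% = 98.05%. The model returned 99.75%, with lower limit 99.1%.

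**Direct standardisation.** The share is 2% by construction. With f = (1 + 5 x correlation)/6, the variance is 0.98² x 0.99 x 0.01 x f/105 + 0.02² x 0.70 x 0.30 x f/14. At expected values the lower 95% limit is 97.3%, 97.1%, 96.9% and 96.7% at correlations 0.2, 0.4, 0.6 and 0.8. Reader variation is not included in this approximation.

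**The case against.** The protocol speaks of a weight per case, not per reading, and leaves detailed methodology to the statistical analysis plan. If the weight acts at patient level, the marginal share is about 2% at every correlation tried. This stands: over-counting of the difficult cases follows only from reading-level weights, and the protocol does not choose between the two. It does not rescue the plan, because 11.2 and 11.5.2 fix the intercept as the tested quantity, and the intercept is not the 98:2 average under a patient-level weight either.

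The correlation is also unknown. That is so, but only values near zero bring the reading-level version back to 2%, and 11.2 says the correlation is high.

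A reader might infer that the trial is underpowered. The documents do not support that. The planned test is on the intercept, and glmer runs of it (60 data sets each) gave joint power of 93%, 98% and 82% at assumed latent correlations of 0.5, 0.8 and 0.95, which brackets the planned 90%. In a separate check with 40 data sets per setting, the sensitivity limit exceeded 95% in 97.5% to 100% of data sets at correlations from 0.2 to 0.8.

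A reader might also infer that the difficult cases always count too much. They do not. A larger patient variance can push the intercept up and hide their misses, as in the 99.75% example. Finally, poor infratentorial results would not go unseen, because 11.5.3 reports that sensitivity separately with its interval. That helps interpretation but does not alter the primary decision rule.

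**Conclusion.** The point holds in this form: the protocol declares a fixed 2% contribution, and the model and read-out it specifies do not deliver a 98:2 average under the high reader correlation it assumes. The realised share of marginal sensitivity is about 2.0% to 8.0% over correlations 0.05 to 0.8 if weights act on readings. It is about 2% if they act on patients, but with a tested intercept of 99.8% or more instead of 98.42%. These figures rest on 105 and 14 evaluable positives, sensitivities of 99% and 70%, the assumed correlation range and, for the quadrature fits, no reader effect.

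The direction of the effect on pass or fail is not fixed; it depends on correlation and software. Nothing here shows that 252 patients is wrong, that the stated power is lost, or that 2% is the wrong value. Specificity carries no such weight and is outside this point.

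**What to change.** In 11.5.2, replace the in-model weight and the intercept read-out for sensitivity by explicit standardisation. Estimate sensitivity separately in the difficult and in the other hemorrhage-positive patients, and combine them on the probability scale as 0.98 x Se(other) + 0.02 x Se(difficult). Take the 95% CI from a method that keeps all six readings of a patient together within each stratum and accounts for readers, for example a stratified patient bootstrap with a reader component. Misses will be few at 99% sensitivity, so the coverage of the interval should be checked in the simulation.

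Re-run the 11.2 simulation with this estimator, state the correlation used, and restate the power it gives.

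The cost is protocol and SAP wording plus simulation work; no new patients, readers or data are needed. The small downside is that the stated power may change.

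### The primary test back-transforms the mixed-model intercept, which is accuracy for a median patient, so FDCT with average sensitivity at or below 95% can be declared non-inferior

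*Protocol*

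**What the plan says.** Protocol section 11.5.2 fits a generalized linear model with a logit link. "The explanatory variables ’reader’ and ’patients’ will be random effects", and "From the fixed-effect intercept of sensitivity and specificity, the 95%-CIs will be calculated applying the method of Wald". The decision follows from that interval: "It will be tested whether both the lower bound of the 95%-CI of the sensitivity and specificity are higher than the margin of 95"%. The synopsis (statistical considerations) repeats the rule.

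Section 11.2 shows that the sample size was simulated with the same quantity: "From the model, the lower end of the 95%-CI of the fixed-effect intercept was extracted and transformed to percent". Neither section averages over the random effects before or after the transformation.

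Section 11.2 also describes the simulated data. True rates were set as follows: "diagnostic performance of hypothetical readers was varied with rates of 98.5%, 99% and 99.5% for sensitivity and 97.5%, 98% and 98.5% for specificity". For agreement between readers, "a high correlation between binary random variables was chosen", without a figure. Sensitivity and specificity are defined there as correct readings divided by the number of cases. Objective 4.2 and hypothesis 11.1 place the 95% margin on the sensitivity and specificity of FDCT.

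**The concern.** In a logit model with random intercepts, the inverse logit of the fixed intercept is the success probability when both random effects are zero, that is, for the median patient and median reader. The proportion of haemorrhages detected is the average of the success probability over all patients and readers. The two coincide only when the random-effect variances are zero. With success rates near 1 the intercept value is the higher one, and the gap grows with the patient variance.

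Patient variance is large exactly when readers tend to miss the same scans. Section 11.2 assumes this and calls it conservative. It may be conservative for the sample size, but it is the least favourable setting for false acceptance, and the protocol reports no check of that.

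At stake is the error rate of the primary conclusion. Section 3.1 says that non-inferiority would support safe triage and that a missed haemorrhage can be lethal. The rule can declare non-inferiority at sensitivities that section 11.1 means to classify as inferior.

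**Working it through.** **Inputs from the protocol (11.2, 11.5.2).** Crossed random intercepts for patient and reader, nloptwrap optimizer, Wald interval on the intercept, margin 95%, 6 readers, 238 evaluable patients in a 1:1 split (119 per group), 14 difficult cases at 70% sensitivity with a total weight of 2%, power 90%, drop-out 5%.

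**Assumption.** The protocol gives no value for the correlation. Readings were generated from a Gaussian copula with latent correlation 0.5, 0.8 or 0.95. At true rates of 98% and 93% these give binary correlations of 0.15–0.23, 0.42–0.49 and 0.69–0.74. A latent value of 0.2 served as a low check.

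**1. The plan's own figures.** 238 / 0.95 = 250.5, which is 252 when rounded up to an even split. This agrees. Simulating the planned rule at the design rates gave:
- latent 0.5: specificity 0.970 × sensitivity 0.990 = 0.96
- latent 0.8: specificity 0.995 × sensitivity 0.980 = 0.975

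This is the right order, but the stated 90% cannot be reproduced exactly because neither the correlation nor the weighting scheme is quantified.

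**2. The shift without any model fitting.** Let b be the intercept and s the patient SD, with no reader variance. The average rate is the integral of expit(b + s·z) over a standard normal z. Solving for b at a fixed average gives:

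| Patient SD | expit(b) at average 95% | expit(b) at average 90% | Average when expit(b) = 95% |
|---|---|---|---|
| 1 | 96.7% | 92.9% | 92.7% |
| 2 | 98.8% | 96.8% | 86.6% |
| 3 | 99.7% | 98.9% | 80.1% |
| 5 | 99.98% | 99.9% | – |

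At an average of 95% these SDs correspond to binary reader correlations of 0.06, 0.23, 0.39 and 0.59. The shift is in the quantity being estimated, so more patients do not remove it.

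**3. Pass rate of the planned rule by true average** (lme4 glmer, 119 patients × 6 readers, 200 replicates; pass if expit(b − 1.96·SE) > 0.95). The comparator is a patient-clustered logit-Wald interval for the average proportion.

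| Latent correlation | True average | Planned rule passes | Median back-transformed intercept | Comparator passes |
|---|---|---|---|---|
| 0.8 | 95% | 100% | 99.99% | 3.0% |
| 0.8 | 93% | 100% | 99.98% | 0% |
| 0.8 | 90% | 98% | 99.96% | 0% |
| 0.5 | 95% | 79% | 99.6% | 2.5% |
| 0.5 | 93% | 47% | 98.5% | 0% |
| 0.5 | 90% | 10% | 96.7% | 0% |

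Further runs with 80 replicates at a true 93% passed 100% at latent 0.95 and 2.5% at latent 0.2. Monte Carlo standard errors reach about 5 points.

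**4. With the 2% weighting kept.** Ordinary cases at 93% and difficult cases at 70% give a weighted average of 0.98 × 93% + 0.02 × 70% = 92.5%. The rule passed 94% of trials at latent 0.8 and 24% at latent 0.5; the comparator passed none.

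**5. A separate simulation by binary correlation** (same model, unweighted, 60 replicates):
- true 95%: 15% at 0.05, 52% at 0.1, 100% at 0.3, 0.5 and 0.7
- true 93%: 65% at 0.3, 100% at 0.5
- true 90%: 23% at 0.3, 97% at 0.5, 100% at 0.7

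**6. The joint rule.** Specificity must also pass, but at its design rates it does so in 99.5% of trials (latent 0.8). Treating the two tests as independent, a true sensitivity of 90% would give a joint success rate of about 0.98 × 0.995 = 0.975.

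**The case against.** **Fitting method.** The protocol names the optimizer but not the likelihood approximation. Under the cruder nAGQ=0 option of the same software (100 replicates), pass rates at latent 0.8 were 93%, 56% and 5% for true averages of 95%, 93% and 90%; at latent 0.5 they were 35%, 2% and 0%. So the size does depend on an unstated setting. The effect is nevertheless not an artefact of the Laplace approximation: a full-quadrature fit with a patient intercept only passed 99%, 100% and 98% at latent 0.8. The inflation at a true 95% appears under every option.

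**Correlation.** It is not stated, and at latent 0.2 the full-quadrature fit passed only 17% at a true 95% and 1% at a true 93%. This stands as a limit on the size, but the protocol assumes high correlation.

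**Reproduction.** The stated 90% power was not matched, and the recomputed power does not clearly fall with correlation as section 11.2 reports. The simulated procedure may therefore differ in detail from the sponsor's. Step 2 does not depend on it.

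**Visibility.** Readings are classified for each reader separately, so a poor raw proportion could be seen beside the test. That does not repair the decision rule.

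**The artificial error.** Section 11.2 says: "In case sensitivity or specificity was 100%, a false negative (for sensitivity) and a false positive (for specificity) was introduced into the generated output". This concerns perfect simulated data sets only and lowers the estimate. It shows that the planned fit is fragile when there are no errors; it does not cause the false passes above.

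**The SAP.** It was not available and might average over the random effects. The protocol does not leave this open, however, and such a SAP would contradict sections 11.2 and 11.5.2.

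**Conclusion.** The concern holds. The quantity tested is not the quantity to which the 95% margin applies, and the error runs in the direction of declaring non-inferiority. At a true average of exactly 95%, where the rule should pass 2.5% of the time, it passed 79% (latent correlation 0.5) to 100% (latent 0.8). At latent 0.8 a scanner missing 5–10% of haemorrhages passes the sensitivity test almost always under Laplace or full-quadrature fitting. The direction is certain whenever the patient variance is above zero. The size rests on the assumed correlation and fitting method: it is large under the protocol's own premise of high correlation and small for true averages of 93% or below when correlation is low. The specificity test has the same defect.

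**What to change.** Replace the intercept rule in the synopsis, 11.2 and 11.5.2 by a test of average sensitivity and average specificity over patients and readers. The interval should account for both kinds of clustering, for example by a two-way bootstrap, an Obuchowski-Rockette variance, or a marginal logit model with cluster-robust errors; the choice among these is secondary. If the mixed model is kept, integrate over the random effects before transforming and bootstrap the bound. Keep the 2% weight for difficult cases, applied on the average scale. Name an exact or Wilson patient-level bound for the case of no errors.

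Then repeat the sample-size simulation with the new estimator, a stated numerical correlation and a stated weighting scheme, and report the pass rate at a true 95% as well as the power.

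The analysis change needs no new data or procedures. The cost is power: at 238 patients and the design rates, the patient-clustered test has joint power of about 0.835 × 0.980 = 0.82 (latent 0.5) or 0.615 × 0.860 = 0.53 (latent 0.8). Holding 90% would need more patients; otherwise the lower power has to be stated.
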